#### Dosso Verde Institute

The Dosso Verde Institute is a Neuropsychiatric Rehabilitation and Psychotherapy Center for Developmental Age. Founded in 1962, the institute provides residential, day, and outpatient services for minors (<18 years) with neurodevelopmental disorders, particularly ASD and intellectual disabilities as well as emotional and behavioral disorders, childhood and adolescent mental health issues, and learning disabilities. The Dosso Verde Institute has facilities in both Pavia and Milan. In the Pavia center, an external catering service is provided, while in Milan, meals are supplied by the internal kitchen of the primary school housed within the same building, “Regina Mundi.”

#### “Giuseppe Garibaldi” Agricultural Technical Institute

The “Giuseppe Garibaldi” Agricultural Technical Institute is a secondary school in Rome, established in 1872. The institute is dedicated to training agricultural experts and technicians knowledgeable in the natural environment. The institute is also home to a boarding school, which accommodates students, including those from nearby schools, who come from distant areas and offers a semiboarding option with lunch services and afternoon study sessions. In the school, meals are prepared daily by a collective catering company.

### Ethical Considerations

This study was approved by the Ethics Committee of the Department of the Nervous System and Behavioral Sciences in January 2024 (approval 155/23). The study adheres to all institutional guidelines and ethical principles outlined in the Declaration of Helsinki. Parents or legal guardians of all participants provided written informed consent before enrollment. They will receive detailed explanations regarding the study objectives, procedures, and potential risks and benefits. Participants will have the right to withdraw from the study at any time without consequences. All collected data will be anonymized and deidentified to protect participant privacy. Identifiable information will be securely stored and accessed only by authorized research personnel. Data will be reported in an aggregate format, ensuring that individual participants cannot be identified.

### Selection Criteria

The target population for the study adheres to the inclusion and exclusion criteria listed in Textbox 1.

Inclusion and exclusion criteria.
**Inclusion criteria**
Presence in medical records of a diagnosis of autism spectrum disorder (ASD; according toDSM-5 [Diagnostic and Statistical Manual of Mental Disorders {Fifth Edition}] diagnostic criteria) including all the 3 severity levels [15].Being a patient of Tiglio Fondazione Onlus in Pavia, Dosso Verde in Milan, and Dosso Verde in Pavia or a student of “Giuseppe Garibaldi” Agricultural Technical Institute in Rome.Children and adolescents aged 3 to 17 years from the Dosso Verde centers in Milan and Pavia, young adults aged 18 to 35 years from Tiglio Fondazione Onlus (Pavia), and high school students aged 14 to 19 years from the secondary school “Giuseppe Garibaldi” Agricultural Technical Institute.Signed informed consent from parents or legal guardians is required for each respondent.
**Exclusion criteria**
Participants who are unable to feed themselves independently due to physical or cognitive impairments.Participants with allergies, intolerances, or conditions requiring a specialized diet.Participants with other neurological or medical conditions (eg, diabetes and epilepsy) that may affect food consumption or require specific medical attention, excluding ASD.

### Recruitment

In Pavia and Milan, care centers with collective catering services were selected, while in Rome, schools offering afternoon activities—including lunch—were chosen. Researchers directly contacted care centers for individuals with ASD and schools offering lunch to present the project. Interested centers in Pavia and a high school in Rome participated in multilevel project presentation sessions. Initially, events targeted health care professionals (child neuropsychiatrists, therapists, and educators) and school staff, followed by meetings with parents. These sessions informed and trained professionals who would act as project supporters and addressed parents’ questions. During parent meetings, informed and privacy consent were collected from parents or legal guardians.

### Study Design

#### Overview

The study will last 36 months (November 2022-2025), including a 12-month experimental phase, from September 2024 until September 2025. Figure 1 shows the study timeline.

**Figure 1 figure1:**
[figure not shown]
Study timeline. CREA: Research Centre for Food and Nutrition; CRF: case report form.

#### Meal Assessment and Menu Adaptation

The study was structured into 3 main phases: scouting, observation, and intervention. After enrolling the participating centers, researchers conducted a preliminary scouting phase by visiting care centers and schools to gain an in-depth understanding of lunchtime dynamics. This phase involved analyzing food service methods, types of cutlery used, staff interaction with participants, and portion sizes served. Based on these observations, portion sizes were standardized according to age groups to ensure consistency in meal assessment and prevent potential biases in data collection. The observation phase (T0) aimed to assess food consumption from standard menus during lunchtime, focusing on both quantity and quality aspects such as sensory characteristics such as shape, color, smell or taste, texture, and temperature. To systematically evaluate these aspects, the pictorial dietary assessment tool (PDAT) was used [16]. Each enrolled participant’s meal was assessed over 3 nonconsecutive days within a 4-week period, with additional sessions scheduled for those absent to ensure complete data collection. A total of 12 PDATs were collected for each participant. To minimize observer influence and reduce bias, researchers passively observed the participants during lunch without direct interaction. They were responsible for completing the PDATs based on observed consumption patterns. To enhance the accuracy of qualitative data, researchers also tasted and photographed each dish to capture its sensory characteristics comprehensively. At the end of each survey day, the research team convened to align on the organoleptic properties of the meals, ensuring consistency in data interpretation. Data entry was performed daily by 3 researchers (CB, SB, and IZ), who decoded the PDATs using a predefined classification system and entered the information into a Microsoft Excel spreadsheet for further analysis. The collected data will serve to compare consumption patterns with sensory characteristics in order to identify key factors influencing meal acceptance. This information will then be used to collaborate with mass catering companies to create dishes aligned with the preferences of individuals with ASD. The authors expect that the sensory modifications will align with those implemented during the FOOD AUT pilot study [6], specifically short pasta shapes (eg, bucatini, penne, orecchiette, and farfalle); foods with low-intensity colors, such as white and beige; uniform hues within the same dish; dishes composed of ingredients with similar, noncontrasting color tones; vegetables that are more readily accepted than orange ones; soft or semisoft textures, avoiding foods that are difficult to chew; mild, nonpungent odors, avoiding strong-smelling foods like certain fish species (eg, mackerel); and delicate flavors, avoiding bitterness and sourness, with reduced use of strong spices, garlic, and onion.

However, the authors consider that having a larger sample than in the pilot study, the most accepted sensory characteristics might be slightly different. The intervention phase (T1) will involve introducing these modified menus and repeating the same assessment process used during T0. Each enrolled participant will undergo the same PDAT-based evaluation over 12 meals to determine whether the targeted menus are better received and lead to increased food consumption.

#### Nutrition Education Course for Parents and Caregivers

Between the T0 and T1 phases, a digital nutrition education course will be offered to subgroups of parents and caregivers of enrolled participants in the Milan and Pavia centers. The course aims to reduce meal-related behavioral difficulties, including FS in individuals with ASD. Participation will be voluntary, following an informational session on the project’s objectives. Designed based on healthy eating guidelines and scientific literature on ASD and nutrition, the course is led by a multidisciplinary team, including a dietitian, nutrition biologists, speech therapists, and a psychologist. It consists of 7 modules delivered through weekly 1-hour sessions, integrating theoretical explanations with practical demonstrations using videos, images, and digital activities. The topics covered in the modules are as follows:

Module 1: the role of nutrition on health and macro- and micronutrients.Module 2: FS: associated factors and consequences.Module 3: healthy plate tailored to the needs of individuals with ASD.Module 4: behavioral strategies for the consumption of nonpreferred foods.Module 5: sensory strategies for the consumption of nonpreferred foods.Module 6: environment and meal presentation.Module 7: mother-child relationship.

To assess the course’s impact and feasibility, specific evaluation tools (detailed in the following section) will be used, along with the recording of attrition rates throughout the program.

### Data Collection

#### Overview

Details of data collected from both participants and their families throughout the study period are presented in the following subsections and summarized in Table 1. Data regarding sociodemographic information, food habits, and feeding behaviors during mealtime were collected through 20- or 25-minute telephone interviews, conducted by a researcher. Data entry is carried out in parallel with data collection, through the daily entry of anonymized data into a preset database.

**Table 1 table1:** Summary of data collection tools.

Tool	Evaluated aspects	Addressed to	Filled out by	T0	T1
CRF^a^	General information of enrolled participants and their families	Parents or caregivers	Researcher (telephone interview)	✓	
KIDMED^b^ [17] (3-24 years) and MEDQS^c^ [18] (25-35 years)	Food habits and adherence to the Mediterranean diet	Parents or caregivers	Researcher (telephone interview)	✓	
BAMBI^d^ [19] (3-11 years) and STEP^e^ [20] (12-35 years)	Risk of food selectivity	Parents or caregivers	Researcher (telephone interview)	✓	
PDTA^f^ [16]	Quantitative and qualitative food consumption	Enrolled participants	Researchers (in presence)	✓	✓
Nutrition knowledge questionnaire	Nutrition course knowledge	Parents or caregivers	Researcher (telephone interview)	Before and after the course	Before and after the course
Satisfaction questionnaire	Nutrition course satisfaction	Parents or caregivers	Researcher (telephone interview)	After the course	After the course

^a^CRF: case report form.

^b^KIDMED: Mediterranean Diet Quality Index for Children and Adolescents.

^c^MEDQS: New Validated Short Questionnaire for the Evaluation of the Adherence of Mediterranean Diet and Nutrition Sustainability in all adult population groups.

^d^BAMBI: Brief Autism Mealtime Behavior Inventory.

^e^STEP: Screening Tool of Feeding Problems.

^f^PDAT: pictorial dietary assessment tool.

#### Sociodemographic Information

Sociodemographic and socioeconomic information of the participants were collected at T0 in a case report form (Multimedia Appendix 1), which was divided into 2 parts. The first part collects data about the participants with ASD: gender, age, ethnicity, and clinical information (drug therapy, therapeutic paths, anthropometric measurements, and blood values), while the second part of the questionnaire aims to gather information about the primary parent, collecting marital status, age, ethnicity, educational level, and therapeutic approaches for managing FS.

#### Food Habits

Information regarding the food habits was assessed at T0. Specifically, the Mediterranean Diet Quality Index for Children and Adolescents questionnaire [17] and the New Validated Short Questionnaire for the Evaluation of the Adherence of Mediterranean Diet and Nutrition Sustainability in all adult population groups questionnaire [18] (Multimedia Appendices 2 and 3, respectively) were used to assess adherence to the Mediterranean diet and to get an overview of the consumption of the main food groups (fruits, vegetables, pasta and cereals, legumes, fish, meat, and dairy products).

#### Feeding Behaviors During Mealtime

Information regarding feeding behaviors during mealtime was assessed at T0. Specifically, Brief Autism Mealtime Behavior Inventory questionnaire [19,20], validated for a population of 3-11 years, and Screening Tool of Feeding Problems questionnaire [21], validated for a population of 12-99 years (Multimedia Appendices 4 and 5, respectively) were used to evaluate dysfunctional meal-related behaviors, including FS of participants with ASD.

#### Meal Assessment

The quantity and quality assessment of meals consumed during lunchtime are conducted using the PDAT [16] at both T0 and T1. Rather than relying on the gold standard weighing method, the PDAT offers a less invasive alternative, allowing for uninterrupted mealtime evaluation. Additionally, when compared to the gold standard, it has demonstrated high accuracy and strong correlations with macronutrient and micronutrient intake [16]. The PDAT consists of 2 sections (Multimedia Appendix 6): a quantitative and a qualitative component, with the latter developed by researchers based on findings from the FOOD-AUT project [6]. The quantitative section enables the monitoring of each meal component (first course, second course, side dish, accompaniment—bread, breadsticks, and crackers—dessert, fruit, yogurt, and beverages) by recording the amount consumed. To facilitate data collection, intake is recorded both numerically (empty plate, one-fourth, half, three-fourth, and fully consumed) and graphically. The graphic representation uses 4 circles (representing a plate divided into 4 sections), which range from white (not consumed) to blue (completely consumed). For beverages, a stylized glass is used, with a gradually increasing water fill indicating empty, one-quarter full, half full, three-quarters full, and full consumption. The qualitative section evaluates the sensory characteristics of each meal component, detailing its shape, color, smell or taste, texture, and temperature. The development of the qualitative part of the PDAT was finalized with the collaboration of a sensory expert, who helped define the possible alternatives for completing each of the main organoleptic characteristics.

#### Nutrition Knowledge

Nutrition knowledge will be assessed in parents and caregivers participating in the nutrition education course. A questionnaire, designed based on the course topics, consists of 21 questions (3 per module; Multimedia Appendix 7). Researchers will administer the questionnaire via telephone interviews before and after the course to evaluate knowledge acquisition.

#### Satisfaction

Satisfaction will be evaluated in parents and caregivers attending the course through a 13-question questionnaire (Multimedia Appendix 8). Administered at the end of the program via telephone interviews, it aims to assess the course’s usefulness, organization, and areas for improvement. Table 1 below summarizes which tools are administered, to whom, with what objective, and at what stage of the project.

### Outcomes and Statistical Analysis

The main outcome of the study testing the improvement of the meal acceptance is an increased food consumption of the proposed targeted meals. Specifically, food acceptance of targeted menus will be calculated as the average intake of the 12 administered set meals, ranging from 0 to 1, comparing results collected at T0 and at T1. The improved food acceptance associated with targeted menus will be estimated assuming a threshold of acceptance of 0.6, calculated as the percentage of cases showing an average PDAT lower than that value. Since the results of the pilot study were encouraging [6], showing an average PDAT greater than or equal to 0.8 in 50% (n=22) of participants, a threshold of 0.6 is assumed as a precautionary measure due to the variability in standard meal composition.

Multiple correspondence analysis at T0 was used to study the association between specific sensory aspects and food consumption, categorized into 5 levels (1=no consumption to 5=total consumption). The analysis produced a map showing the distances between the categories of the qualitative variables and food consumption levels.

Concerning the subgroup of caregivers attending the nutrition education course, statistical analysis will focus on effectiveness evaluation of the course, measured by the comparison of nutrition knowledge score, the prevalence of FS score, and the adherence to the Mediterranean diet score before and after the education intervention and by the dropout rate at the end of the course.

Since no preliminary information is available on the average consumption and variability of the PDAT, the determination of sample size is made on the expectation of a possible decreased propensity of FS. FS is an attitude found in 80% of the population with ASD, starting as early as childhood [6]. Hence, setting a significant level of α=.05 and a test power of 90%, under the assumption that the rate of FS may decrease to 15 percentage points, namely from p(T0)=80% to p(T1)=65%, 150 participants could be sufficient [22].

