Collective catering is a critical setting too, as many adults with ASD consume their meals in the care centers where they reside, while children and adolescents have at least 1 meal a day at school. This setting opens a potential opportunity for intervention that, if properly exploited, can enable an improvement in the nutritional status of individuals with ASD through specifically formulated menus, leading to a cascade of beneficial effects on their health [1]. There are currently no specific guidelines about how to customize collective catering menus for participants with ASD in Italy. In fact, due to the specificity of the target population and the complexity of working with individuals affected by ASD, no multicenter studies aimed at improving food acceptance have so far been carried out on large groups across different age ranges.

The authors designed and conducted a pilot study, the FOOD-AUT project [6], in which canteen menus were adapted to meet the nutritional and sensory needs of adults with ASD, with the aim of reducing their FS and consequently improving their health. The study involved 22 participants and focused on adapting meals based on key sensory characteristics, such as texture, color, and shape, to enhance food acceptance. The results showed that personalized meal modifications could positively influence dietary variety and meal consumption in individuals with ASD. Since the pilot study was conducted in a single setting with a limited sample size, this study, the AUT-MENU project (improving the meal acceptance of participants with ASD), aims to extend the same model to multiple contexts, including care facilities and schools, to further evaluate its effectiveness. This broader implementation will strengthen the dataset and provide more robust evidence, ultimately supporting the development of specific dietary guidelines for collective catering services tailored to individuals with ASD.

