## Methods

### Study Overview

The AUT-MENU study is a single-arm pre- and postbicentric intervention study (without control). The study is conducted by a multidisciplinary team consisting of researchers from the Laboratory of Dietetics and Clinical Nutrition of the University of Pavia and the Research Centre for Food and Nutrition of Rome.

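### The main outcome has two unranked summaries, mean intake and the share below 0.6; improvement is tied to the second, which is less powerful and whose direction is unclear

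*Protocol article*

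**What the plan says.** All of this stands in the protocol article, mostly under Outcomes and Statistical Analysis.

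- **First summary.** Food acceptance is "calculated as the average intake of the 12 administered set meals, ranging from 0 to 1, comparing results collected at T0 and at T1".
- **Second summary.** The next sentence reads "The improved food acceptance associated with targeted menus will be estimated assuming a threshold of acceptance of 0.6", and continues "calculated as the percentage of cases showing an average PDAT lower than that value".
- **Reason for the cut-off.** The pilot is described as "showing an average PDAT greater than or equal to 0.8 in 50% (n=22) of participants", after which "a threshold of 0.6 is assumed as a precautionary measure due to the variability in standard meal composition".
- **Pilot size.** Background states: "The study involved 22 participants".
- **Design.** Study Overview: "The AUT-MENU study is a single-arm pre- and postbicentric intervention study (without control". Each participant is therefore their own comparator.

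The section also says that no advance information exists on average PDAT consumption or its variability. The sample size of 150 is therefore built on the rate of food selectivity, not on either PDAT summary. The selection criteria (Textbox 1) do not require food selectivity for entry.

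**The concern.** Two definitions of the main outcome stand side by side, and the text does not say which one decides whether the menus worked. Improvement is attached to the dichotomised one. Three things follow.

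1. Whichever summary looks better could become the headline after the data are seen.
2. If the 0.6 share is the test, only participants who cross 0.6 count. A person who moves from 0.65 to 0.85, or from 0.30 to 0.50, adds nothing. Anyone already above 0.6 on the standard menu cannot improve at all.
3. Improved acceptance is expressed as the percentage falling below the acceptance threshold. Taken literally, a larger value would mean worse acceptance. A fall in that share, or a rise in its complement, is presumably meant, but the article does not say so.

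The reason given for 0.6 does not settle the matter. The same cut applies at T0 and T1, so a lower cut is not cautious for the comparison between them. It enlarges the group that starts above the cut.

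**Working it through.** **The plan's own figure.** The 150 reproduces as the number per group for two independent proportions, one-sided α=0.05, power 90%, with pooled variance under the null:

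n = {[1.645·√(2·0.725·0.275) + 1.282·√(0.80·0.20 + 0.65·0.35)] / 0.15}² = [(1.039 + 0.798)/0.15]² ≈ 150.

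It concerns food selectivity (80% to 65%). It does not depend on the 0.6 cut, so it says nothing about the power of either PDAT summary.

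**Check 1: analytic efficiency of a cut (normal model).** The article gives neither the T0–T1 correlation r nor the share p below 0.6, so both are varied.

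Unpaired efficiency relative to the mean is φ(z_p)²/[p(1−p)]:
- p=0.50: 0.64
- p=0.35: 0.60
- p=0.20: 0.49
- p=0.10: 0.34

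For paired data (two-sided 0.05, 90% power), let d = z_p0 − z_p1, let δ be the fall in the share below the cut, and let p_d be the discordant proportion:
- N(mean) = 2(1−r)(1.960+1.282)²/d²
- N(McNemar) = {[1.960√p_d + 1.282√(p_d−δ²)]/δ}²

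Example: an assumed fall in the share below the cut from 80% to 65%, with r=0.5. Here d = 0.842−0.385 = 0.456 and p_d ≈ 0.296. The mean needs 51 participants and McNemar needs 134, an efficiency of 0.38. Over r:

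| r | N, 0.6 share | N, mean | Efficiency |
|---|---|---|---|
| 0 | 188 | 101 | 0.54 |
| 0.3 | 157 | 71 | 0.45 |
| 0.5 | 134 | 51 | 0.38 |
| 0.7 | 108 | 31 | 0.28 |

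For an assumed fall from 50% to 35%, efficiency runs from 0.62 (r=0) to 0.34 (r=0.7). Over the wider set of assumptions examined, the information lost is roughly 36% to 80%.

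**Check 2: simulated power.**

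Inputs from the article:
- 12 meals per phase, intake bounded at 0 and 1, cut at 0.6;
- n=74 (enrolled in Pavia and Milan) and n=150 (stated sample size).

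Assumed inputs:
- between-person SD 0.20, meal-to-meal SD 0.25;
- mean gain 0.08 with SD 0.15 between persons;
- T0 centre (before capping at 0 and 1) from 0.4 to 0.8.

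Tests: paired t-test against asymptotic McNemar, two-sided 0.05, 3,000 replicates. Repeat runs differ by one or two points.

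| T0 centre | Below 0.6 at T0 | n=74: mean vs share | n=150: mean vs share |
|---|---|---|---|
| 0.4 | 83% | 98% vs 82% | ~100% vs 99% |
| 0.5 | 69% | 94% vs 75% | ~100% vs 97% |
| 0.6 | 51% | 92% vs 57% | ~100% vs 86% |
| 0.7 | 33% | 87% vs 27% | 99% vs 55% |
| 0.8 | 18% | 81% vs 10% | 98% vs 20% |

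The mean has more power in every row. The gap is small at n=150 when most participants start below 0.6, and very large when most start above it.

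**Check 3: the pilot figure.** 50% of 22 is 11. If 22 were instead the number who reached 0.8, the pilot would need 22/0.5 = 44 participants, against the 22 given under Background.

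**The case against.** The strongest reply is that the mean has not been given up. It is defined first and compared between T0 and T1, so the 0.6 share may be meant only as a responder summary beside it. This stands. A reader might infer that the dichotomy replaces the mean, but the text does not say so. The defect is the missing ranking, together with the attachment of improvement to the weaker summary. Which tests will be used is a detail an article may leave to the full plan, and its absence is not held against it here.

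A reader might also infer that the cut throws away most of the information. That is not established. The loss depends on a distribution and a correlation that the article does not give, and at n=150 with low T0 intake almost no power is lost. The n=74 results also describe enrolment before Rome had begun, with about 200 participants envisaged in the Abstract.

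A third tempting inference is that the pilot result was miscounted. The documents do not support this either. The 22 can be read as the denominator, which agrees with Background, and 0.6 is not calculated from it. The notation is merely ambiguous.

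Finally, a lower cut is easier for an individual to reach, but it applies at both times, so it does not by itself bias the comparison in favour of the menus. What remains is that calling it precautionary is unsupported.

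**Conclusion.** The point holds as one of ranking, direction and efficiency. The article states two versions of the main outcome without saying which is primary, and words the second in a direction opposite to improvement.

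If the 0.6 share is the test, the power lost ranges from slight (about 100% vs 99%, n=150, T0 centre 0.4) to severe (81% vs 10%, n=74, centre 0.8). All of these figures rest on the assumed SDs, gain and T0 level. A severe loss requires many participants to be above 0.6 already on standard menus. The documents neither state nor exclude this, and it is possible because food selectivity is not an entry criterion.

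**What to change.** - **Primary outcome.** Name the within-participant change in 12-meal mean PDAT (T1 minus T0) as the single primary outcome. Analyse it with a paired comparison or a linear mixed model with a participant random intercept and site as a fixed effect. If individual meals rather than phase means are modelled, let the T0–T1 effect also vary by participant, so that differences in gain between people enter the standard error.
- **Secondary summary.** Keep the 0.6 share as secondary and state its direction: either the share at or above 0.6, or a fall in the share below it.
- **Cut-off.** Give a reason for 0.6 that bears on the T0–T1 comparison, or drop the description of it as precautionary.
- **Pilot figure.** Say whether it means 11 of 22.

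The change costs some rewording and routine modelling of data already being collected. The one small downside is that the headline becomes a gain in mean intake rather than a percentage of responders.

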**Methods:**

The study is a bicentric intervention conducted in 3 care centers (Pavia and Milan) and 1 secondary school (Rome), involving approximately 200 participants with ASD aged 3 to 35 years. The study consists of an observational phase (T0) and an intervention phase (T1). At T0, biographical data, clinical characteristics, and dietary patterns of participants are collected. Based on T0 findings and existing nutritional recommendations for individuals with ASD, targeted menus are developed and tested. At T1, the same assessment tools used at T0 will be applied to evaluate intervention effects. Additionally, a nutrition education course for caregivers will be implemented between T0 and T1, with a pre- and postcourse knowledge questionnaire to assess its effectiveness.

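### The T0 sensory analysis, as described, does not separate a sensory attribute from the meal component that carries it, yet it is used to name drivers of acceptance and to inform the T1 dishes

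*Protocol article*

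**What the plan says.** Under Outcomes and Statistical Analysis, the protocol article names one analysis linking sensory attributes to intake: "Multiple correspondence analysis at T0 was used to study the association between specific sensory aspects and food consumption, categorized into 5 levels". The next sentence gives its output: "The analysis produced a map showing the distances between the categories of the qualitative variables and food consumption levels". Both sentences are in the past tense.

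Under Meal Assessment, the data are described at a finer level. On intake: "The quantitative section enables the monitoring of each meal component (first course, second course, side dish, accompaniment", with the list continuing to dessert, fruit, yogurt and beverages. On attributes: "The qualitative section evaluates the sensory characteristics of each meal component, detailing its shape, color, smell or taste, texture, and temperature". Meal component is therefore available in the data for every intake score and every attribute.

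Under Meal Assessment and Menu Adaptation, the purpose is stated: "The collected data will serve to compare consumption patterns with sensory characteristics in order to identify key factors influencing meal acceptance". The use follows directly: "This information will then be used to collaborate with mass catering companies to create dishes aligned with the preferences of individuals with ASD". The abstract adds a second source for the menus: "Based on T0 findings and existing nutritional recommendations for individuals with ASD, targeted menus are developed and tested". Primary Objectives likewise cites existing guidance, and Meal Assessment and Menu Adaptation expects the changes to resemble those of the pilot. Principal Findings carries the sensory results forward into advice for collective catering.

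**The concern.** In a set canteen lunch, sensory attributes are unlikely to be spread evenly over the courses. Pasta and bread tend to be pale and mild; vegetable sides tend to be coloured and stronger in taste. The article itself ties attributes to food type: Background says that avoiding strong colours and odours leads to whole food groups being left out, with canned fish and certain vegetables as examples.

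If participants eat most of their first course and leave their vegetables for any reason, a map of attributes against intake that ignores course will place pale and mild near full consumption. It will do so even if colour and flavour make no difference among first courses or among sides.

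The stated purpose is to find what influences acceptance, which is a causal reading of a descriptive map. At stake is whether the modifications made to particular dishes, and the guidance later given to caterers, are based on attributes that matter within those dishes.

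**Working it through.** **What can be checked.** The article reports no coordinates, no intake by attribute and no cross-tabulation of attribute by course. Its one design figure, the sample size of 150, concerns the prevalence of food selectivity and does not enter here. The check is therefore an illustration on assumed inputs.

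**Step 1: what the method sees.** Multiple correspondence analysis (MCA) is built from the pairwise cross-tabulations of the variables entered. Unless the analysis is run by course, the table of colour against intake level is summed over courses. Entering course as a further variable would plot it as extra points, but the colour-by-intake table would still be the pooled one. Only stratification or adjustment gives the within-course association.

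**Step 2: size of the false association.** Let course *c* have frequency w, mean intake m (0 to 1) and share of pale dishes q, with no colour effect within any course. Then:

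- pooled intake, pale = Σ w·q·m / Σ w·q
- pooled intake, other = Σ w·(1−q)·m / Σ w·(1−q)

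Assumed: five equally frequent courses.

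| Course | m | q, strong link | q, weak link | q, no link |
|---|---|---|---|---|
| First | 0.80 | 0.70 | 0.55 | 0.50 |
| Second | 0.65 | 0.50 | 0.50 | 0.50 |
| Side | 0.35 | 0.10 | 0.40 | 0.50 |
| Bread | 0.85 | 0.95 | 0.60 | 0.50 |
| Fruit | 0.50 | 0.30 | 0.45 | 0.50 |

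The equal weights cancel, and Σm = 3.15.

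- Strong link: Σq = 2.55 and Σqm = 0.560 + 0.325 + 0.035 + 0.8075 + 0.150 = 1.8775. Pale = 1.8775/2.55 = 0.736. Other = (3.15 − 1.8775)/(5 − 2.55) = 1.2725/2.45 = 0.519. Gap 0.217.
- Weak link: Σq = 2.50 and Σqm = 0.440 + 0.325 + 0.140 + 0.510 + 0.225 = 1.640. Pale = 1.640/2.50 = 0.656. Other = 1.510/2.50 = 0.604. Gap 0.052.
- No link: both are 0.630. Gap 0.

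The gap within each course is 0 in all three cases by construction.

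**Step 3: does an MCA map show it?** One data set was simulated under the strong link, with 74 participants (the number enrolled in Pavia and Milan) × 12 meals (the number of PDATs per participant) × 5 courses = 4,440 records. Intake levels were drawn as binomial out of 4 with the means above. Texture was also given course-dependent shares and no effect within course. The MCA used colour, texture and the five intake levels. Positions on dimension 1 (the sign is arbitrary):

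| Category | Dimension 1 |
|---|---|
| Pale | −0.79 |
| Full consumption | −1.06 |
| Not pale | +0.81 |
| No consumption | +1.47 |

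Pale falls on the side of full consumption and not pale on the side of none. In the same data the pooled gap was 0.206, while the five within-course gaps lay between −0.024 and +0.004. The map shows a colour pattern where none exists within any course.

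**The case against.** The strongest reply is that this argues from silence. The article gives the MCA two sentences and never says that courses were pooled. Component-level data exist, and a map by course would be compatible with the text. That stands in part: pooling is inferred from the variables named, and a by-course map may have been made. But the article does not leave this analysis to another document. It reports it as done, with its variables and its output, and course appears in neither.

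A reader might also infer that the map decides the T1 menus. It does not: existing recommendations and the pilot's changes are further sources, and some of those changes already concern one food type (pasta shapes, vegetables, fish).

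A reader might infer that the menus will drift towards starch, or that altering the colour or texture of a side dish cannot raise its intake. Neither is supported. The article speaks of modifying dishes, including vegetables, and continues to record each component at T1. A zero effect within course is an assumption of the illustration, not a finding.

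Nor is the primary comparison undermined. Average intake at T0 against T1 tests the menus as a package, whichever attributes shaped them.

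Finally, stratifying by component is an incomplete remedy: within sides, colour and bitterness still travel with the particular vegetable. That stands, and it limits what the fix can deliver.

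**Conclusion.** The point holds in a limited form. As described, the T0 map cannot distinguish a sensory attribute from the meal component that carries it, and the article puts a stronger reading on it than such a map can bear. Component is already recorded, so a better analysis is available.

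The size is unknown. On the assumed inputs the false gap runs from 0, if attributes are unrelated to course, to about 0.2 on the 0-1 intake scale, if they are strongly related. The documents do not give the attribute-by-course distribution needed to place the study in that range. The conclusion also assumes that the analysis was run as the article describes it, without strata.

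The damage is confined to which attributes are chosen for modification and credited with acceptance, and to the guidance drawn from them. It should be corrected, but it is not a threat to the T0-T1 result.

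**What to change.** State whether the T0 MCA was run by meal component. If it was not:

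- repeat the sensory analysis within each component, or model intake on the attributes with adjustment for component;
- rest conclusions about attributes, and the final catering guidance, on the within-component associations;
- use those associations as the T0 input to the Rome menus, where enrollment had not begun, and to any other menus not yet fixed;
- report the pooled map as descriptive only, and soften the wording about factors that influence acceptance accordingly.

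No new data are needed, since the T0 PDAT records from Pavia and Milan were entered daily. The intervention phase there was scheduled for April to June 2025, so those menus may already be fixed; the re-analysis would then still serve Rome and the final guidance. The price is fewer distinct dishes per component, so some attributes cannot be judged in every component. Confounding by the specific food within a component may remain and should be acknowledged.
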